#### Secondary outcomes

The secondary outcomes include the number of follicles ≥ 14 mm, E2 level, and endometrial thickness on the hCG trigger day; the number of retrieved oocytes, metaphase II (MII) oocytes, and two pronuclei (2PN) fertilizations; as well as the rates of 2PN fertilization, available embryos, high-quality embryos, implantation, cycle cancellation, biochemical pregnancy, pregnancy loss, sustained pregnancy, and live birth. The outcomes of IVF-ET and their definitions are summarized in **Table 4**. While the post-treatment observation will be terminated at about 24 weeks, data on live birth will be obtained through the participating centers’ mandatory, complete follow-up system extending to the end of pregnancy.

**Table 4 T4:** Diagnosis definitions of IVF-ET outcomes.

Diagnosis	Definition
Primary outcomes	
clinical pregnancy rate (CPR)	the number of clinical pregnancies divided by the total number of embryo transfer cycles.
Secondary outcomes	
Outcomes of IVF-ET	
2PN fertilization rate	the number of 2PN embryos divided by the number of MII oocytes
available embryo rate	the number of transferable embryos divided by the number of 2PN fertilization
high-quality embryo rate	the number of high-quality embryos divided by the number of normally fertilized cleavage embryos. High-quality embryos were defined based on the day of embryo transfer, according to the Istanbul consensus and Gardner criteria, as follows: Day 2: embryos with 4 cells, <10% fragmentation, and absence of multi-nucleation; Day 3: embryos with 8 cells, <10% fragmentation, and no multi-nucleation; Day 5: blastocysts at stage 4, with inner cell mass and trophectoderm both graded as A (17, 18).
Implantation rate	the number of gestational sacs divided by the number of embryos transferred.
cycle cancellation rate	the number of cancelled embryo transfer cycles divided by the number of embryo transfer cycles
biochemical pregnancy rate	the number of patients with positive serum b-hCG pregnancy test results divided by total embryo transfer cycles
pregnancy loss rate	the number of pregnancy termination cycles within 12 weeks divided by the number of embryo transfer cycles
sustained pregnancy rate	the number of cycles of pregnancy greater than 12 weeks divided by the number of embryo transfer cycles
live birth rate	the number of live births divided by total embryo transfer cycles.
Scale measurement	
self-rating anxiety scale (SAS)	SAS consists of 20 items, and its measurement is determined by calculating the sum of the scores of each item

Additionally, ovarian reserve will be assessed using AFC and serum levels of AMH, FSH, LH, and E2. AFC and serum levels of FSH, LH, and E2 will be measured on days 2 to 5 of the menstrual cycle, while AMH can be measured on any day of the menstrual cycle. These assessments will be conducted both before and after the acupuncture intervention, with the post-intervention assessment scheduled during the menstrual period of the IVF cycle.

Anxiety levels will be evaluated using the Self-Rating Anxiety Scale (SAS). The total SAS score reflects the severity of anxiety symptoms, with a standard cutoff score of 50 used to classify participants into four categories: no anxiety (<50), mild anxiety (50–59), moderate anxiety (60–69), and severe anxiety (≥70) (19). The SAS will be performed before the first acupuncture session and within 24 hours after the final session.

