#### Inclusion criteria

Women meeting the diagnostic criteria for DOR (13) and scheduled for IVF-ET will be enrolled provided they fulfill all the following conditions:

Age 20–39 years;AFC<5, AMH<1.2 ng/mL (13);With regular menstrual cycles (21–35 days);With GnRH antagonist or microstimulation protocol for controlled ovarian hyperstimulation (COH);Plan to transfer 1–2 high-quality cleavage embryos or one blastocyst;Able and willing to give written informed consent.

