### Outcome measurement

#### Primary outcome

The primary outcome is the CPR following the first fresh or frozen embryo transfer. Ultrasonographic identification of a gestational sac and fetal heartbeat at 28 days post-embryo transfer confirmed a clinical pregnancy. The CPR is defined as the proportion of clinical pregnancies to the total number of embryo transfer cycles.

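### The high-quality embryo rate changes its numerator standard with the day of transfer over a fixed denominator, so a different transfer-day mix between arms would bias this secondary comparison

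*Protocol article*

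**What the plan says.** The definition is in Table 4 of the protocol article, under Secondary outcomes. The rate is "the number of high-quality embryos divided by the number of normally fertilized cleavage embryos". The rule that sets the standard for the numerator is that "High-quality embryos were defined based on the day of embryo transfer". Three standards are listed. An embryo needs 4 cells under the day-2 rule and 8 cells under the day-3 rule, in both cases with fragmentation below 10% and without multinucleation. The third standard is "Day 5: blastocysts at stage 4, with inner cell mass and trophectoderm both graded as A".

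The design leaves the stage and type of transfer open. Inclusion criteria has "Plan to transfer 1–2 high-quality cleavage embryos or one blastocyst", and Primary outcome has "The primary outcome is the CPR following the first fresh or frozen embryo transfer". Randomization method places allocation after consent and stratifies by age only. The Acupuncture group section has treatment running for roughly ten weeks, up to oocyte retrieval. Table 4 also lists a cycle cancellation rate, so cycles without a transfer are expected. Statistical analysis applies intention-to-treat to all analyses. It reserves the covariate-adjusted model for the primary outcome and compares other outcomes with t, Wilcoxon, chi-square or Fisher tests.

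**The concern.** A rate meant to compare embryo quality between arms should apply one yardstick to every embryo. Here the yardstick depends on the transfer day, while the denominator stays at the cleavage stage. Under the day-5 rule the result mixes two things: how many embryos reach the blastocyst stage, and how good those blastocysts are. Under the day-2 and day-3 rules it reflects cleavage-stage appearance alone.

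The actual transfer day comes after randomisation and after the treatment under test. Oocyte and embryo yield are themselves trial outcomes. If yield influences the transfer day, a treatment effect on yield could change which standard is applied. The rate could then move between arms with no difference in embryo quality. If the day-5 standard is the harder one to meet, the arm with more day-5 transfers would look worse. Nothing stated for secondary outcomes adjusts for this.

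A smaller gap concerns women who have fertilised embryos but no transfer. They have no transfer day from which to pick a numerator standard.

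**Working it through.** The plan states no figure for this rate, so there is nothing to reproduce. The check has two parts.

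**1. Reading the definition against the design**

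| Element | What the protocol article fixes | Depends on transfer day? |
|---|---|---|
| Denominator (Table 4) | Cleavage embryos that fertilised normally | No |
| Numerator standard (Table 4) | Day 2, day 3 or day 5 criterion | Yes |
| Transfer stage (Inclusion criteria) | Cleavage or blastocyst | Left open |
| Transfer type (Primary outcome) | Fresh or frozen | Mapping to day 2, 3 or 5 not given |
| Time of transfer | After randomisation and treatment | – |
| Women with embryos and no transfer | Denominator exists | Numerator standard has no day |

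One cohort of embryos can therefore have two different rates, depending only on when a transfer takes place.

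**2. Illustration of the artefact, with identical embryos in both arms**

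All inputs are assumptions, because the documents give none:

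- q3: share of the denominator embryos that meet the day-3 standard, 30–50%.
- q5: share of the same embryos that meet the day-5 standard, 5–20%.
- f: share of embryos graded by the day-5 rule, which may differ by arm.

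Expected rate in an arm = (1 − f) × q3 + f × q5.

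Difference between arms = (fA − fB) × (q5 − q3).

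Central example, with q3 = 40% and q5 = 10%:

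- f = 20%: 0.8 × 40% + 0.2 × 10% = 34%.
- f = 40%: 0.6 × 40% + 0.4 × 10% = 28%.
- Difference: 6 percentage points with no true difference in quality.

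Size of the artefact in percentage points:

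| Day-5 share, arm A vs arm B | q3 = 30%, q5 = 20% | q3 = 40%, q5 = 10% | q3 = 50%, q5 = 5% |
|---|---|---|---|
| Equal | 0 | 0 | 0 |
| 20% vs 30% | 1 | 3 | 4.5 |
| 20% vs 40% | 2 | 6 | 9 |
| 10% vs 50% | 4 | 12 | 18 |

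The equal-share row shows that the bias needs a difference in transfer-day mix. The calculation holds embryo quality constant across transfer days. If quality and transfer day are related, the size would change.

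**The case against.** The strongest reply is that the transfer-day phrase is loose wording for the embryo's culture day. The three standards are developmental stages, and a frozen transfer has no calendar day 2, 3 or 5, which favours that reading. On that reading the gaps for frozen transfers and for women without a transfer close. The text does not say this, however. Even so read, three unequal standards would still share one cleavage-stage denominator, with no rule for an embryo observed on both day 3 and day 5.

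Three stronger readings are tempting, and the documents do not support them:

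- A reader might infer that the rate is undefined for women without a transfer. Their denominator does not depend on a transfer, and nothing in Table 4 excludes them. Only the numerator criterion lacks a day.
- A reader might infer that the transfer day is picked with the embryos in view. No section says who sets the day, when, or on what basis. Eligibility requires a transfer plan, so some intention exists at entry. What stands is that the realised day falls after randomisation.
- A reader might infer that the comparison cannot be interpreted. With an equal mix the expected artefact is zero. Participants and efficacy evaluators are blinded, and the unblinded acupuncturists take no part in outcome evaluation, so an imbalance would have to come mainly from treatment or chance.

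It can also be said that the Quality control section refers to procedures for outcome assessment, and that a condensed article leaves grading detail to them. That is fair for how embryos are recorded. It does not cover a rule the article itself states.

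**Conclusion.** The point holds in a limited form. As written, Table 4 lets identical embryos score differently according to a post-randomisation event, and the comparison of this rate is biased if the arms differ in transfer-day mix. No evidence in the documents shows that they will differ. The 2 to 9 points for day-5 shares of 20% and 40% show what is arithmetically possible under the assumed pass rates, not a likely size in this trial. The direction (lower rate in the arm with more day-5 transfers) rests on the assumption that fewer embryos meet the day-5 standard than the day-3 standard. The missing numerator criterion for women with embryos but no transfer is a literal gap that sits badly with intention-to-treat, and multiple imputation cannot supply a definition. This is one of many secondary outcomes, so the matter is a worthwhile clarification and not a threat to the trial's main conclusion.

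**What to change.** Amend Table 4 before the data are analysed:

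1. Define a cleavage-stage high-quality rate, graded on one fixed culture day with the plan's own criterion (for example its day-3 standard). The denominator is all cleavage embryos that fertilised normally, whether or not they are transferred, so women without a transfer are included.
2. Define a separate blastocyst quality rate with the plan's day-5 standard, over embryos taken to extended culture. That denominator is itself selected after randomisation, so the rate is best read descriptively.
3. Report embryos transferred or frozen on day 2 separately with the plan's day-2 standard.

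The cost is a wording change and the use of laboratory records. No treatment or transfer decision is altered. The downside is that embryos transferred or frozen on day 2 have no day-3 grade, so some dependence on transfer or freezing day remains. Separate reporting makes that visible but does not remove it.

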### Blinding assessment

Upon completion of the full acupuncture treatment, participants in both the two groups will be surveyed on the oocyte retrieval day to guess their group assignment, thereby testing the blinding integrity.

### Assessment of safety

Adverse events (AEs) will be systematically monitored and recorded throughout the trial. AEs will be classified by severity (mild, moderate, severe) and causality (divided into 5 levels: definitely unrelated, probably unrelated, possibly related, probably related, definitely related) (20). All events will be documented in the case report form (CRF) with details on the exact time of onset, interval from needling, manifestations, management, and outcome, with causality judged by the acupuncturist.

Acupuncture-related AEs, potentially including hematoma, bleeding, subcutaneous hemorrhage, severe pain, local infection, and fatigue, will be collected at each treatment session. AEs associated with IVF-ET encompass pain, organ injury, colporrhagia, infections secondary to oocyte retrieval procedures, ovarian hyperstimulation syndrome (OHSS), thrombosis, allergic reactions, post-transplant abdominal pain, breast swelling, frequent urination, and nausea. All AEs will be characterized by the principal investigator and an independent data-safety monitor in terms of severity, causality, seriousness, and outcome, with serious ones requiring immediate reporting to the institutional review board within 24 hours.

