## Introduction

Diminished ovarian reserve (DOR) is a momentous contributing factor of female infertility, defined by a reduction in oocyte quantity and/or quality, its diagnostic biochemical profile typically includes elevated serum follicle-stimulating hormone (FSH), alongside decreased levels of anti-Müllerian hormone (AMH) and a less antral follicle count (AFC) (1). The pathogenesis of DOR is associated with multiple factors, including age, genetic, iatrogenic, autoimmune, infectious agents, environmental, and social-psychological (2). Epidemiological data from 2004–2011 showed DOR prevalence rising from 19% to 26% (3). DOR usually leads to unsatisfactory outcomes in *in vitro* fertilization-embryo transfer (IVF-ET). DOR patients achieve lower clinical pregnancy rates (CPR) and live birth rates (LBR) during IVF-ET than those without DOR (4, 5).

The subpar response of DOR patients to exogenous gonadotropins poses a major challenge in the field of reproductive endocrinology (6). Elderly individuals and those with elevated basal FSH levels often display poor responsiveness to ovulation induction due to their diminished ovarian reserve (6). Although various interventions, including growth hormone (GH) and dehydroepiandrosterone (DHEA), have shown potential to optimize ovarian performance and reproductive outcomes in assisted reproduction (6–8). Presently, the effectiveness of these treatment modalities has not been definitively confirmed due to insufficient robust clinical trials.

Acupuncture is regarded as a beneficial alternative therapy for DOR (2). Although further high-quality studies are warranted, accumulating evidence demonstrates that acupuncture effectively modulates reproductive hormone profiles (9), enhances ovarian reserve function (10, 11), increases CPR (10, 11), and reduces anxiety (12) in women undergoing IVF-ET. Given these beneficial effects on ovarian reserve parameters and IVF-ET outcomes, acupuncture represents a promising therapy for DOR.

Accordingly, we initiated a prospective, multicenter, randomized controlled trial to rigorously assess both the efficacy and safety of acupuncture for DOR patients undergoing IVF-ET. The primary outcome is the CPR following the first embryo transfer.

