#### Blinding

Blinding procedures will be implemented for study participants, efficacy evaluators, and statistical analysts. Given the inherent characteristics of acupuncture, there is no blindness for acupuncturists. The acupuncturists will not participate in any baseline assessment, randomization procedures, or outcome evaluation of the participants.

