This study possesses several constraints. Initially, it will encompass solely DOR women aged < 40 who are eligible for either GnRH antagonist protocols or microstimulation protocols, which might diminish the representativeness of the sample population. Secondly, owing to the intrinsic characteristics of acupuncture, operator-blinding is not feasible in this trial comparing acupuncture and placebo acupuncture.

In conclusion, this trial employs a rigorous and well-established acupuncture protocol for the treatment of DOR. The results may support acupuncture as a viable treatment for DOR patients.

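### Adverse-event causality is given to the unblinded acupuncturist in one sentence and to the principal investigator and safety monitor in another, and the protocol does not say which grade governs

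*Protocol article*

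**What the plan says.** Three statements in the protocol article bear on who grades causality.

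- **Assessment of safety, first paragraph.** Events are graded for severity and for "causality (divided into 5 levels: definitely unrelated, probably unrelated, possibly related, probably related, definitely related". All events go into the case report form with a factual description, "with causality judged by the acupuncturist".
- **Assessment of safety, second paragraph.** "All AEs will be characterized by the principal investigator and an independent data-safety monitor in terms of severity, causality, seriousness, and outcome". The acupuncturist is not mentioned here.
- **Blinding.** "Blinding procedures will be implemented for study participants, efficacy evaluators, and statistical analysts". By contrast, "there is no blindness for acupuncturists". The section then adds: "The acupuncturists will not participate in any baseline assessment, randomization procedures, or outcome evaluation of the participants".

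The Introduction makes safety an aim of the trial, which is set up "to rigorously assess both the efficacy and safety of acupuncture for DOR patients undergoing IVF-ET". The Discussion concedes as a limitation that "operator-blinding is not feasible in this trial comparing acupuncture and placebo acupuncture", but does not connect this with the grading of adverse events.

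**The concern.** Causality on a five-level scale is a judgement. The first paragraph gives it to the person who delivers the treatment and knows whether the needle went through the skin. Such a grader may, without intending to, be readier to attribute fatigue, pain or bleeding to treatment in the acupuncture arm than in the placebo arm.

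The second paragraph assigns the same judgement, for the same events, to two other people. As written, two causality grades can exist for one event, and the text neither ranks them nor says how to settle a disagreement. With 13 centres, local practice could differ. If the choice between the grades is left until the data are reviewed, it could be made with both sets in view.

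What is at stake is the comparison of treatment-related events between arms, in a trial that names safety as an aim.

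**Working it through.** This point has no formula, and the plan gives no figure to reproduce. The check is a comparison of the text.

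**Step 1. Do the two sentences in Assessment of safety cover the same thing?** Yes. Each covers all adverse events and each assigns causality. The first names the acupuncturist; the second names the principal investigator and an independent safety monitor. Neither refers to the other, and neither is called provisional or final.

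**Step 2. Is the first-named judge blinded?** No. Blinding says so directly, and the Discussion repeats it.

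**Step 3. Are the second-named judges blinded?** The document does not say. The blinded roles in Blinding are participants, efficacy evaluators and statistical analysts. No safety assessor is on that list, so the second paragraph cannot be taken to supply a masked grade as it stands.

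**Step 4. Is there real room for judgement?** Yes, for part of the events. Treatment runs up to the day of oocyte retrieval (Acupuncture group), so needling and IVF procedures overlap in time. The two lists in Assessment of safety overlap in kind: pain, bleeding and infection appear, in one form or another, both as acupuncture-related events and as IVF-related events. For such events the causality grade bears on whether they count against acupuncture. The arms also differ visibly to the operator: one is needled through the skin, to 60–70 mm at BL33 (Table 2), while the other has no skin penetration at any point (Table 3).

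**Step 5. Which results depend on the grade?** Only the division of events into related and unrelated. The number of events, their severity and their seriousness do not use it. Nor does the primary outcome, which rests on ultrasound (Primary outcome).

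**Step 6. Can the effect be sized?** No. Suppose each arm had the same number *n* of ambiguous events, and the grader called a proportion *a* related in the acupuncture arm and *b* in the placebo arm. The spurious difference would be *n*(*a* − *b*) events. It is zero if *a* = *b* and can be no larger than *n*. The documents give none of the three quantities, so any single worked example would only return the values put into it.

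**The case against.** The best defence is that the two paragraphs describe two stages. The acupuncturist, who is present, makes the source entry; the principal investigator and the safety monitor then review every event. Both sentences can be true at once on that reading, and the second stage is a safeguard. This largely answers any claim that the paragraphs cannot be reconciled. It does not settle the point, because the text does not say that the review overrides the first grade or that the reviewers are masked.

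A reader might also infer that the plan flatly contradicts its Blinding section. The documents do not support that. The bar is on outcome evaluation, and adverse events are not among the outcomes under Outcome measurement; they have a section of their own. The assessors listed as blinded are those of efficacy. Because safety is a stated aim, grading causality fits poorly with the spirit of the bar, but a narrower reading is open.

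Two further inferences go too far. One is that the whole safety comparison is biased; Step 5 limits it to the related/unrelated split. The other is that acupuncturists will grade differently by arm; the text supports only that they may.

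Finally, which causality variable enters the safety tables is ordinarily a matter for the analysis plan, which is not shown, and its absence here is no fault in itself. The point does not rest on that absence. It rests on a rule the article does state: that an unblinded treatment provider judges causality, followed by a second rule naming other judges.

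**Conclusion.** The point holds in limited form. The article gives a subjective grade to an unblinded treatment provider, then assigns the same grade to two other roles, and does not say which governs. If the acupuncturist's grade is analysed, the between-arm split of related and unrelated events may be biased by knowledge of allocation. If the later review governs and is masked, most of the concern falls away, but the article states neither.

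The size of any bias is unknown. Events that leave little doubt about their cause should be little affected; the exposure lies in ambiguous events such as fatigue, pain and bleeding. The conclusion assumes that related events will be compared between arms, which the safety aim implies but the Statistical analysis section does not spell out. The text should be corrected, but the point does not threaten the primary result.

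**What to change.** Reconcile the two sentences in Assessment of safety:

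1. The acupuncturist records only the facts: when the event began, how long after needling, what was observed and how it was managed. If a causality view from the acupuncturist is kept, label it provisional.
2. State that the causality grade used in the analysis is the one made by the principal investigator and the independent safety monitor, and say how a disagreement between them is settled.
3. State that they grade, where feasible, from a record that does not show the arm, and add this role to the Blinding section.

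**Cost.** A short change to the protocol and to the instructions for completing the case report form, using roles already named. It is not entirely free: someone must remove the arm, and details that give it away, from the record passed to the graders. Masking will also be incomplete, because needle-site events such as a hematoma may reveal the arm. That limit should be acknowledged in the report. It is no reason to leave the ambiguous events to an unblinded grader.
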